### Outcome measure

The primary endpoint is the change in pulmonary vascular resistance between baseline and 12 months. Secondary endpoints include several clinical and quality-of-life parameters (as detailed in Table 2).

**Table 2 Tab2:** Secondary endpoints, exploratory endpoint and safety evaluation that will be measured and/or compared at baseline and at 12 months after initiation of treatment

Secondary endpoints	
Change in hemodynamic variables	mean pulmonary arterial pressure, cardiac output, etc.
Change in 6-min walk distance	
Change in WHO functional class	
Change in plasma NT-proBNP level	
Change in echocardiography	tricuspid annulus systolic displacement (TAPSE), right atrium area, right ventricle size, eccentricity index, pericardial effusion
Change in Borg dyspnea index	
Change in quality-of-life parameters (SF 36)	
**Exploratory endpoint**	
cardiopulmonary exercise testing	
cardiac magnetic resonance	
**Safety evaluation**	
Frequency of adverse events	hemoptysis/pulmonary hemorrhage (vascular perforation, vascular dissection, vascular rupture, etc), pneumothorax, hypotension, pulmonary congestion/ pulmonary edema, late-onset lung disturbance, heart failure, pneumonia, headache, dizziness, peripheral edema, nausea/vomiting, retching, diarrhea, nasopharyngitis, upper respiratory inflammation, respiratory distress, coughing and fainting
Clinical worsening during the observation period and time to clinical worsening	All-cause mortality, heart/lung transplant, hospitalization due to clinical worsening, new initiation of pulmonary hypertension target medications, worsening of 30% or greater from baseline in the 6MWD and persistent worsening in the WHO FC from baseline due to the worsening of a primary disease.
Laboratory tests	hemoglobin, alanine aminotransferase, creatinine, aspartate aminotransferase

### Data collection and management

The investigators who enter information into the case report form (CRF) are responsible for ensuring the accuracy and completeness of information. The investigators must save the CRF and all the original data. According to CRF data, a database is established through Epidata software. Data collection and management are carried out by physicians who are blinded to this trial to avoid bias. Linkable anonymization by central registration number is used to identify the subjects and only the subject number is recorded in the case report form. Moreover, when a patient’s name appears in any other document (such as a pathology report), the name must be hidden before providing a copy of the document. The investigators are responsible for the appropriate storage of the correspondence table prepared by them to identify the subjects. This correspondence table must be retained for 5 years after completion of this study. Appropriate measures, such as encoding or deletion, are taken to ensure that the subjects cannot be identified in any display or public disclosure of information related to this study, in accordance with applicable laws and regulations. If data are transmitted over an unsecured electronic network, the data must be encoded at the source. Representatives of the clinical research office, ethics committee/institutional review committee, and relevant supervision and management departments have the right to inspect medical records to verify the collected data. During the inspection process, the above-mentioned personnel strictly follow the local data protection laws to keep the subjects’ personal information confidential.

If the results of the study are published publicly, the information confirming the identity of the subject remains confidential.

### Frequency and plans for auditing trial conduct

Auditors will verify adherence to required clinical trial procedures and will confirm accurate data collection according to the Good Clinical Practice (GCP) guidelines. Study monitoring and follow-up, from the initial setup to final reporting, will be fulfilled according to current National and International requirements.

### Provisions for post-trial care

Before study entry, potential participants are informed via the consent form that they will be offered post-trial treatment according to routine clinical practice.

### Adverse events

The occurrence of any untoward medical events, including complications or the worsening of pre-existing underlying diseases, is defined as adverse events. Worsening of efficacy evaluation indices is not defined as adverse events. Any concomitant symptoms or clinically significant abnormal fluctuations in test results are investigated to determine whether there is a cause-and-effect relationship with BPA or riociguat, and findings are documented in the CRF. Adverse events are followed up until normalization or recovery to a level not considered to be an adverse event, or in the case of an irreversible adverse event (cerebral infarction, myocardial infarction, etc.), until symptoms stabilize.

### Statistical analysis

Data analysis is performed by a specific specialized investigator who keeps being blind to the trial. The research measurement data are presented as mean ± standard deviation, and count data are presented as frequency or percentage. In the baseline characteristics of patients, count data are compared using Pearson’s *χ*^2^ test or Fisher’s exact test and measurement data are compared using *t* test. For primary analysis, the least square means difference and 95% CI for change of pulmonary vessel resistance between groups at 12 months are estimated using analysis of covariance adjusted for allocation factors. For patients who withdraw from the study, the last observation carried forward (LOCF) before withdrawal is used for statistical analysis. Adverse events are evaluated during the safety analysis. The frequencies of adverse events are compared using Fisher’s exact test. We consider the *p* value < 0.05 of two-sided test to be statistically significant. All statistical analysis is performed using SPSS software V22.0. The statistical analysis plan is developed by the principal investigator and biostatistician before the completion of patient recruitment and data fixation.

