## Methods and analysis

### Design

This study is a singer-center, prospective, randomized controlled trial. As shown in Fig. 1, subjects willing to consider enrollment are consented prior to invasive evaluation. Subjects undergo V/Q scan, right-heart catheterization, and pulmonary angiography for definitive diagnosis of CTEPH by the standard practice based on ESC guideline recommendation [3]. The identified CTEPH patients are provisionally enrolled in this study. An independent experienced PEA surgeon determines if subjects are eligible for PEA. If the subjects are deemed technically operable, they are excluded from this study. All patients who meet the inclusion criteria but don’t meet the exclusion criteria are randomly divided into two groups with 2:1 rate via a randomization application and are observed for 12 months. One group is treated with riociguat only, namely the riociguat group (R group); the other group is given additional BPA therapy on the basis of 3 months riociguat treatment, which is riociguat + BPA group (R+B group). Riociguat tablets are administered orally to all randomized patients at starting dose of 1.0 mg TID and are increased by 0.5 mg increments in 2-week intervals to 1.5, 2.0, and 2.5 mg TID (maximum total daily dose: 7.5 mg) if systolic blood pressure (SBP) is ≥ 95 mmHg and there are no signs or symptoms of hypotension. If higher doses are not tolerated, patients are maintained on lower doses (minimum allowed dose: 0.5 mg TID). After the end of the 8-week titration phase, riociguat is continued at the optimal individual dose for 4 weeks. In the R+B group, patients receive 4 times BPA in 2–3-week intervals in the following 3 months according to the morphology of the pulmonary lesion evaluated by preoperative right-heart catheterization and pulmonary angiography. In general, 3 vessels are performed each time. However, at least among the collaborative institutions included in this study. PEA-inoperable patients are very rarely considered unsuitable for BPA, because the institutes are professional BPA centers in China. Then all participants are followed up to 12 months. And the safety follow-up is up to 30 days later the study completion.

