**Fig. 1 Fig1:**
[figure not shown]
Flow diagram of study recruitment and randomization. After obtaining consent and diagnosis of chronic thromboembolic pulmonary hypertension is confirmed, subjects will be randomized into either the B+R or R group, to receive treatment for 12 months. Patients in the B+R group receive 4 times BPA 3 months later initial riociguat in 3 months. Observations will be recorded at the time of screening/baseline and at 3, 6, and 12 months after the initiation of treatment. BPA, balloon pulmonary angioplasty; CTEPH, chronic thromboembolic pulmonary hypertension

Observations are made at the time of screening or baseline and 3, 6, and 12 months after initial treatment. All BPA procedures are performed by two specific surgeons who are blinded to the trial, and echocardiography, 6MWD, and cardiopulmonary exercise testing are performed by specific experienced physicians who are blinded to the trial.

Data processing of patients who withdraw from the study or terminate the study uses the last measured value (LOCF) before withdrawal for statistical analysis. Table 1 shows the schedule of assessments performed at each visit for each treatment group, including mandatory and optional assessments.

**Table 1 Tab1:** Schedule of visits and observation items for enrolled subjects

Observation items	Visit 1 Screening/baseline	Visit 2 3 months ± 7 days	Visit 3 6 months ± 7 days	Visit 4 12 months ± 7 days
Informed consent	X			
Inclusion/exclusion	X			
Demographics	X	X	X	X
Medical history	X	X	X	X
vital signs	X	X	X	X
Laboratory tests	X	X	X	X
Blood gas test	X	X	X	X
electrocardiogram	X	X	X	X
6MWD	X	X	X	X
WHO-FC	X	X	X	X
Pulmonary function	X			X
Echocardiography	X		X	X
RHC	X			X
CPET	X		X	X
CMR	X		X	X
QOL (SF-36)	X	X	X	X
Concomitant medication	X	X	X	X
Medication adherence		X	X	X
Adverse events	X	X	X	X

*6MWD* 6-min walk distance, *WHO-FC* World Health Organization functional class, *RHC* right-heart catheterization, *CPET* cardiopulmonary exercise testing, *CMR* cardiac magnetic resonance, *QOL* quality of life

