### Sample size

Previously, BPA shows to result in reducing pulmonary vascular resistance from 7.3±3.2 WU to 3.8±1.0 WU (mean ± SD) within 6 months [15], while riociguat is reported to decrease pulmonary vascular resistance by 2.83±3.1 WU [6]. Based on these studies, it is assumed that the change in mean pulmonary vascular resistance from the start of treatment to 12 months after treatment would be − 4.5 WU for the BPA+R group and − 2.8 WU for the R group, with SD of 2 and 2, respectively. The minimum sample size requires to achieve a significance of 0.05 from a two-sided test with a statistical power of 90%. The combination group is determined to be 54 subjects, and the riociguat group is 27 subjects, for a total of 81 subjects. We estimate the dropout rate to be 15%.

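### LOCF is fixed for a primary endpoint scheduled only at baseline and month 12, so on scheduled data a withdrawal before month 12 counts as zero PVR change and planned power is lost

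*Protocol article*

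**What the plan says.** Under Outcome measure, "The primary endpoint is the change in pulmonary vascular resistance between baseline and 12 months". Table 1 marks right-heart catheterization (RHC), the source of PVR, at Visit 1 (baseline) and Visit 4 (12 months), and leaves the 3- and 6-month visits blank.

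The missing-data rule appears twice. The Design section, in the text before Table 1, says that data processing for patients who withdraw or terminate "uses the last measured value (LOCF) before withdrawal for statistical analysis". The Statistical analysis section repeats it directly after the primary analysis: "For patients who withdraw from the study, the last observation carried forward (LOCF) before withdrawal is used for statistical analysis". Neither place makes an exception for PVR. The article mentions no RHC at withdrawal and no alternative analysis.

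The PVR differences "are estimated using analysis of covariance adjusted for allocation factors". The Sample size section assumes mean changes of -4.5 WU (BPA plus riociguat, R+B) and -2.8 WU (riociguat, R), "with SD of 2 and 2, respectively", with "significance of 0.05 from a two-sided test with a statistical power of 90" percent. It gives 54 + 27 = 81 subjects and an estimated dropout of 15%.

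**The concern.** LOCF needs an intermediate value to carry. For PVR the schedule has none, so the last scheduled value before a withdrawal is the baseline value, and baseline minus baseline is zero. Zero is not a neutral guess here, because the plan expects both arms to improve substantially.

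Two things follow. The arm expected to improve more loses more per withdrawal, so equal dropout shrinks the estimated effect. Mixing zeros with values centred at -4.5 or -2.8 also widens the spread. The sample size allowance for dropout covers neither effect: it replaces lost patients, but the analysis keeps those patients as zeros. At stake are the planned power of the primary comparison and, if withdrawal differs by arm, the size and even the direction of bias in the primary estimate.

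**Working it through.** **Inputs (Sample size and Design sections):** mean changes -4.5 and -2.8 WU (difference 1.7), SD 2 in each arm, two-sided 0.05, power 90%, allocation 2:1, N = 54 + 27, dropout 15%.

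**Step 1: reproduce 81.** An exact two-sample t-test with difference 1.7 and SD 2 needs 46 + 23 = 69 patients (power 90.7%). Dividing by the retention rate, 69/0.85 = 81.2. So 81 reproduces, within rounding, as a total that already includes 15% dropout treated as lost information. With no dropout, 54 + 27 gives about 95% power.

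**Step 2: the effect of zeros.** If a fraction p of an arm with mean m is scored 0:
- arm mean = (1-p)m
- arm variance = (1-p) x 4 + p(1-p)m²

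At p = 0.15 in both arms:
- R+B: mean 0.85 x (-4.5) = -3.825; variance 3.4 + 0.1275 x 20.25 = 5.98; SD 2.45
- R: mean 0.85 x (-2.8) = -2.38; variance 3.4 + 0.1275 x 7.84 = 4.40; SD 2.10
- difference = 1.445 WU (that is, 0.85 x 1.7)
- SE = √(5.98/54 + 4.40/27) = 0.523
- z = 1.445/0.523 = 2.76; power = Φ(2.76 - 1.96) = 79%

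A simulation of 40,000 trials gives 74% with the pooled t-test and 77% with the Welch test. The pooled test does worse because the larger arm now has the larger variance.

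**Step 3: range over equal dropout (54 + 27).**

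| Dropout in each arm | Difference (WU) | Power, simulated pooled t | Power, normal approximation |
|---|---|---|---|
| 5% | 1.615 | 89% | 91% |
| 10% | 1.53 | 82% | 85% |
| 15% | 1.445 | 74% | 79% |

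Under this rule about 114 patients would be needed for 90% power at 15% dropout (normal approximation).

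**Step 4: if 81 is the number before inflation.** Enrolment would be 81/0.85 = 95.3, so 96 (64 + 32). With 15% zeros, simulated power is about 82% (pooled) to 84% (Welch), still below 90%.

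**Step 5: type I error.** Set both true means to -2.8.
- Equal dropout: the expected difference is 0, and simulated rejection at 15% is about 5%.
- Unequal dropout, an assumed split of 10% R+B and 25% R, which is (5.4 + 6.75)/81 = 15% overall: means are 0.90 x (-2.8) = -2.52 and 0.75 x (-2.8) = -2.10, a spurious difference of -0.42 WU. SE = √(4.31/54 + 4.47/27) = 0.495, and rejection is about 14%.
- The reverse direction, assumed 20% R+B and 5% R (also 15% overall), under the planned effect: 0.80 x 4.5 - 0.95 x 2.8 = 0.94 WU instead of 1.70.

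**The case against.** **The power loss depends on actual dropout.** This stands. At 5% in each arm power is still about 89%, close to plan. But 15% is the protocol's own figure.

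**The comparisons above are unadjusted, while the plan uses ANCOVA.** This stands in part. Covariates may recover some precision, but they do not correct outcome values that were set to zero by rule.

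**An analysis plan not shown may handle missing data differently.** The article does promise such a plan. LOCF, however, is a rule stated in the protocol in two places and not a gap left for later.

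**A reader might infer that the rule inflates false positives as it stands.** The documents do not support that. They give one dropout figure and no split by arm. With equal dropout the type I error stays near 5%, and the 14% figure needs an assumed imbalance.

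**A reader might also infer that R+B withdrawals carry forward a treated PVR from a BPA session while R withdrawals carry baseline.** The article does not say so. Its reference to lesions "evaluated by preoperative right-heart catheterization and pulmonary angiography" can mean the diagnostic study before treatment. The limitations section says operators know the PVR, not that it is re-measured or entered as trial data. BPA also starts only after 3 months of riociguat, so earlier withdrawals could have no session value. If every R+B withdrawal did carry a treated value, with 15% dropout in each arm and no true difference, the bias would be -2.8 - (0.85 x -2.8) = -0.42 WU. If half did, it would be -0.21 WU.

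**Deaths.** The listed withdrawal criteria are patient request and investigator judgement. Whether a death is scored as zero change is not stated, although the Design wording on termination could be read that way.

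**Conclusion.** The concern holds for scheduled data: a withdrawal before month 12 is scored as zero PVR change, against the plan's own expectation for both arms. At the plan's 15% dropout, taken as equal in the two arms, the expected difference is 1.45 instead of 1.70 WU and unadjusted power about 74-79% instead of 90%. These figures rest on the plan's means and SD, on withdrawals having the same underlying outcomes as completers, and on 81 already including the 15%, which the arithmetic supports but the text does not say. If 81 excludes it, power is about 82-84%.

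The certain harm is attenuation and lost power under equal dropout. Bias away from the null and excess false positives are possible only if dropout differs by arm or if session PVR exists and is carried forward. The documents establish neither. Nor do they support saying that every withdrawal must be scored zero, since the existence of unscheduled PVR values is left open. The rule should be changed before analysis, because it acts directly on the primary estimate.

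**What to change.** 1. Remove LOCF for the primary endpoint in both places, the Design section and the Statistical analysis section.
2. Analyse all randomised patients with the planned ANCOVA, with missing month-12 PVR multiply imputed by arm from baseline PVR and a small set of measures already scheduled at months 3 and 6, such as 6-minute walk distance and WHO functional class.
3. State that any unscheduled PVR obtained at BPA sessions is not carried forward as the outcome.
4. Add one sensitivity analysis that does not assume missing at random, for example control-based or delta-adjusted imputation.

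The cost is revised wording and a little more analysis work; no new data are needed. The downside is a modelling assumption that rests on few patients: at 15% dropout the riociguat arm has about 27 x 0.85 = 23 completers, so the imputation model must stay small. Patients who leave before month 3 contribute only baseline information to it.

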## Discussion

2015 ESC/ERS Guidelines for the diagnosis and treatment for pulmonary hypertension, 2018 Cologne Consensus, and 2018 Chinese pulmonary hypertension diagnosis and treatment guidelines recommend riociguat and BPA for patients with inoperable CTEPH [3–5]. Sequential treatment with riociguat and BPA for patients with inoperable CTEPH shows significant improvements in mean pulmonary arterial pressure and pulmonary vascular resistance [18]. Case report shows hybrid of riociguat and BPA therapy in CTEPH patient improved echocardiographic parameters of RV function [19]. A randomized controlled trial comparing riociguat and BPA (the RACE study) is being conducted in France (https://clinicaltrials.gov/ct2/show/NCT02634203). A multicenter randomized controlled trial to compare BPA versus riociguat in patients with CTEPH is ongoing [20]. However, there is no report directly comparing treatment outcomes of BPA combined riociguat and riociguat alone. Therefore, this study is planned to compare the efficacy and safety of BPA combined with riociguat and riociguat alone for inoperable CTEPH.

According to the current guidelines, the diagnosis of CTEPH requires at least 3 months of anticoagulation. Therefore, 3 months is set as the anticoagulation course for newly diagnosed patients with suspected CTEPH to exclude patients with subacute thrombosis. For CTEPH patients who have been previously diagnosed and have been anticoagulated for a long time, they can be directly evaluated. The primary endpoint of this study is the change in pulmonary vascular resistance from baseline to 12 months, as this is an important factor to decide the severity of CTEPH. Other outcomes often used in studies on CTEPH, such as the 6MWD and mean pulmonary arterial pressure, are secondary endpoints in this study. In this study, 4 times BPA treatment is completed in 3 months and 3 vessels are performed each time, which is in keeping with real-world practice in China. This study also evaluate the long-term efficacy and safety of BPA combined with riociguat and riociguat alone by continuing evaluations for 12 months after initiation of treatment. In addition, the operability of PEA is determined by an independent experienced PEA surgeon who belongs to an independent institute. This avoids recruitment bias and guarantees reliability in this study. Furthermore, this study compares patient-reported quality-of-life and the parameters from CMR. These factors may contribute to optimizing treatment strategies and following-up strategies for inoperable CTEPH. The results of this study are disseminated at medical conferences and in journal publications.

### Strengths and limitations of this study

This is a randomized controlled trial comparing the efficacy and safety of BPA combined with riociguat and riociguat alone in patients with inoperable chronic thromboembolic pulmonary hypertension. This study evaluates the efficacy and safety of BPA combined with riociguat over a relatively long period (12 months). This is the first study to compare the efficacy and safety between BPA combined with riociguat and riociguat alone.

The main limitation of this study is the open-label trial design. Because there is no distinct criterion for BPA in each lesion, operators are aware of the mean pulmonary vascular resistance (the primary endpoint in this study), and they might be incentivized to continue BPA. Thus, the bias for the BPA operators cannot be completely avoided. However, since this study compares medical and surgical treatment, it is difficult to use a placebo or mask patients and/or physicians. Other limitations of this study include single-center design and a relatively small number of subjects are recruited.

## Data Availability

The main trial datasets generated and/or analyzed during the current study are not publicly available while the study is underway due to the sensitivity of the data, but are available from the corresponding author on reasonable request. Data is however available from the authors upon reasonable request and with permission of the Shanghai Pulmonary Hospital Database.
